#### Interim analyses

No interim analyses will be performed.

#### Analyses of safety endpoints

Absolute and relative frequencies of all safety endpoint events will be displayed for the whole population and separately for experimental and control group and will be compared using chi-squared tests.

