**Methods:**

This is a randomized, prospective, multicenter, open-label, controlled, parallel-group interventional trial to test the adjunctive effect of TPE in patients with early septic shock. Patients with a refractory (defined as norepinephrine (NE) ≥ 0.4 μg/kg/min ≥ 30 min OR NE 0.3 μg/kg/min + vasopressin) and early (shock onset < 24 h) septic shock will be included. The intervention is a standard TPE with donor fresh frozen plasma (1.2 × individual plasma volume) performed within 6 h after randomization and will be compared to a standard of care (SOC) control arm. The primary endpoint is 28 days mortality for which the power analysis revealed a group size of 137 / arm (*n* = 274) to demonstrate a benefit of 15%. The key secondary objective will be to compare the extent of organ failure indicated by mean SOFA over the first 7 days as well as organ support-free days until day 28 following randomization. Besides numerous biological secondary, safety endpoints such as incidence of bleeding, allergic reactions, transfusion associated lung injury, severe thrombocytopenia, and other severe adverse events will be assessed during the first 7 days. For exploratory scientific analyses, biomaterial will be acquired longitudinally and multiple predefined scientific subprojects are planned. This study is an investigator-initiated trial supported by the German Research Foundation (DFG, DA 1209/7–1), in which 26 different centers in Germany, Switzerland, and Austria will participate over a duration of 33 months.

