#### Safety endpoints

The following safety endpoints are assessed until day 7 following randomization (Table 1): bleeding complications, thrombotic complications, allergic reactions, infections related to the entry site of the dialysis catheter or new bloodstream infections, transfusion related lung injury, occurrence of, and time to severe thrombocytopenia (< 5.000/μl) and other device related serious adverse events (SAEs). Given the profound severity of disease in the patients under investigation (hospitalized patients under critical care, shock and (multi) organ failure) a variety of AEs and SAEs are expected to incept as part of the natural history of disease and will therefore not be reported. Furthermore, SAEs, that are not directly related to critical illness / sepsis per se and are classified as possibly, probably, or causally provoked by the intervention, will additionally be recorded until day 7. Potential SAEs that are directly related to critical illness will thus not be explicitly reported.

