### Sample size

The primary aim of the study is to demonstrate superiority of SOC + TPE compared to SOC alone with regard to the primary endpoint 28-day mortality. In a prospective, monocentric, non-controlled pilot study of the TPE treatment in patients with septic shock, the observed 28-day mortality rate was 65%, while the predicted mortality rate using the APACHE-II-score was as high as 91% [10]. Meanwhile, two randomized clinical trials have been conducted. In one (small, *n* = 20 vs 20) randomized control trial, the observed mortality rate of the TPE-treated patients was 40% in contrast to 50% in the control group, resulting in a risk difference of − 10% with a 95% CI of [− 0,41;0,21] [14]. In another randomized control trial, the observed mortality rate of the treated patients was 33.3 and 53.8% in the control group, resulting in a risk difference of − 21% with a 95% CI of [− 0.39; − 0.02] [8]. For sample size calculation, we considered the two RCTs only and combined the outcome in a meta-analysis. The treatment procedures were similar, and the two trials are very homogeneous (I2 of 0%). The meta-analysis resulted in a risk difference of − 18% with a 95% CI of [− 0.34; − 0.02]. This risk difference was used in the sample size calculation. Sample size calculation was done for a two-group continuity corrected chi-square test (Query Advisor 8.7.1.0). To detect a reduction in 28-day mortality rate from 60 to 42% in the experimental group with a two-sided type I error rate of 5% and a power of 80%, at least 131 patients per group are required. Thus, the total sample size to detect the expected effect on the 28-day mortality is 262 patients. Stratification for sex, center, pulmonary focus of infection (yes/no), and lactate (< / ≥ 4.5 mmol/) at randomization is assumed to increase power of the statistical test. Considering a drop-out rate of 5%, a total of 274 patients will be assigned to the trial, i.e., recruited.

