### Statistical methods

#### Analyses populations

The intention-to-treat (ITT) population comprises all randomized patients. Patients will be analyzed as randomized independently of the performed intervention. Primary analyses of all efficacy endpoints will be conducted on the ITT population.

The per-protocol (PP) population comprises all patients that received the randomized intervention and were complying with the study protocol until the end of the follow-up period. Supplementary efficacy analyses will be conducted on the PP population.

The safety population comprises all patients that received the study intervention. Patients will be analyzed as treated. Analyses of safety endpoints will be conducted on the safety population.

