## Discussion

To the present time, no adequately powered randomized clinical trial has investigated the effect of TPE on survival in septic shock patients. Previous studies investigating TPE in sepsis have either been underpowered or included a heterogenous study population [7, 8]. Therefore, despite promising data demonstrating more rapid hemodynamic stabilization [10, 14], the role of TPE as a potential adjunctive treatment option in septic shock remains unclear. As we have observed the most obvious clinical effects (during the feasibility trial) in sepsis patients that have been treated very early after onset of shock and that demonstrated particularly profound hemodynamic instability, we have designed the inclusion criteria of the here described study accordingly. This effort to homogenize the participants (early and severe septic shock) stands in contrast to previous trials that have investigated a broader range of septic patients.

TPE using human plasma as replacement fluid has potential adverse effects, including infectious and non-infectious (allergic reaction, transfusion associated lung injury (TRALI), citrate toxicity, hypotension) [16] with pruritus and urticaria most commonly observed [17]. However, severe adverse events are extremely rare [18] and incidence of adverse events requiring discontinuation of treatment lies at around 0.2% [17]. Of note, no adverse events were observed in our previous EXCHANGE feasibility pilot study [10] and the randomized EXCHANGE-1 trial, investigating patients with literally the same characteristics [19]. To avoid potential allergic reactions, anti-histamines will be administered before TPE (and in the control group at time of randomization). Importantly, there is no additional invasive exposure of the patient. The central line used for TPE will be inserted for clinical management (e.g., RRT) only and all biosamples will be drawn via catheters (central venous and arterial), which have been placed independent of biosampling for treatment and monitoring indication. Therefore, no additional puncture of the skin needs to be performed for biosampling.

The investigators convinced that a risk–benefit consideration clearly favors performance of the here proposed clinical trial. Importantly, this is an investigator-initiated trial, funded by the DFG without any competing commercial or financial interests involved.

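### Chi-squared tests are the only named between-arm comparison for safety; for uncommon harms they would usually miss a doubling of risk, so risk differences with confidence intervals should be reported

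*Protocol article*

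**What the plan says.** The section Analyses of safety endpoints is one sentence. What it tabulates is counts and percentages of events, and of these it says that they "will be displayed for the whole population and separately for experimental and control group and will be compared using chi-squared tests". It names no effect measure, interval or alternative method for sparse counts.

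The sentence covers a broad list. Under Safety endpoints: "The following safety endpoints are assessed until day 7 following randomization (Table 1): bleeding complications, thrombotic complications, allergic reactions". The list goes on to infection at the catheter site or in the bloodstream, lung injury after transfusion, very low platelet counts and serious events linked to the device. Other serious adverse events attributed to the intervention are also recorded to day 7.

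On expected frequency, the Discussion says of plasma exchange: "However, severe adverse events are extremely rare". It puts adverse events that lead to discontinuation at around 0.2%. No control-arm rate is given for any safety endpoint.

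The sample size serves 28-day mortality: "with a two-sided type I error rate of 5% and a power of 80%, at least 131 patients per group are required", and after allowance for drop-out "a total of 274 patients will be assigned to the trial"; the abstract's power analysis "revealed a group size of 137 / arm". On who is counted for safety: "The safety population comprises all patients that received the study intervention", analysed as treated.

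**The concern.** A chi-squared test answers whether the observed difference is surprising if there is no true difference. For harms, the reader mainly needs to know how large an excess the data still allow. When events are uncommon and the sample is set by a large mortality effect, the two answers diverge: the p-value will often be large while a clinically relevant excess remains possible. When no events occur, the test returns nothing, although the data do bound the difference.

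The article says that a positive result could change standard of care. Readers would then weigh a mortality benefit against bleeding, thrombosis, infection and lung injury, and would need an estimate with its uncertainty for each. The article gives interval-based criteria for mortality and mean SOFA, but for safety it names only a test.

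**Working it through.** **Inputs.** From the article: 1:1 allocation; 274 randomised, so 274 / 2 = 137 per arm; two-sided 5% as for the primary endpoint. Assumed: control event rates of 1% to 20%, because none is given.

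**The plan's own figure.** For 60% against 42% mortality, with Δ = 0.18 and mean rate 0.51:

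n = [1.960·√(2·0.51·0.49) + 0.8416·√(0.60·0.40 + 0.42·0.58)]² / 0.18² = (1.3856 + 0.5853)² / 0.0324 = 119.9.

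With continuity correction: (119.9/4)·[1 + √(1 + 4/(119.9·0.18))]² = 130.8, that is 131 per group, as stated. The trial is therefore sized for an 18-point difference in a common event.

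**Power of the safety test.** The Pearson statistic is X² = (x₁ − x₂)²/n² ÷ [p̄(1 − p̄)·2/n], where p̄ is the pooled proportion, and is significant above 3.84. All pairs of binomial counts with n = 137 per arm were enumerated, without continuity correction, and only rejections in the direction of harm were counted.

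| Control → TPE | Power | Missed | Per arm for 80% power |
|---|---|---|---|
| 1% → 2% | 8% | 92% | 2319 |
| 2% → 4% | 14% | 86% | 1141 |
| 5% → 10% | 35% | 65% | 435 |
| 10% → 20% | 65% | 35% | 199 |
| 20% → 40% | 96% | 4% | 82 |

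With continuity correction the first four powers fall to 2%, 8%, 27% and 58%. With 131 per arm and no correction, 5% → 10% has 34% power, so the exact size of the safety population matters little. A harm absent in controls is detected with 80% power once the TPE rate is about 4%.

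**What an interval adds (illustrative counts, 137 per arm).**

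- 14 against 7 events: p̄ = 21/274 = 0.0766; X² = (7/137)² / (0.0766·0.9234·2/137) = 2.53, p = 0.11. The risk difference is 7/137 = +5.1 points. The 95% score (Miettinen-Nurminen) interval runs from −1.3 to about +12 points; the Newcombe-Wilson interval is −1.4 to +11.8.
- 6 against 3 events: p = 0.31; risk difference +2.2 points, Newcombe-Wilson interval −2.5 to +7.3.
- 0 against 0 events: p̄ = 0, so X² is 0/0 and undefined. The Wilson upper limit in each arm is (3.84/137)/(1 + 3.84/137) = 2.7%, so the interval is −2.7 to +2.7 points.

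**How sparse the data may be.** At the article's 0.2% rate, the chance of at least one event among 137 TPE patients is 1 − 0.998¹³⁷ = 24%. That rate refers only to events leading to discontinuation of plasma exchange; it is not a background rate for bleeding or thrombosis.

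**The case against.** The strongest reply is that this is a superiority trial with no safety hypothesis, reported in a condensed article. Interval estimates for safety tables are commonly left to the SAP, and low power for rare harms affects any trial of this size and is not cured by a change of analysis. That last part is right: the fix does not raise power; it makes the remaining uncertainty visible. The rest does not dispose of the point, because the article is not silent: it names a method, and that method is a poor fit for these endpoints.

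Five stronger readings are tempting, and the article does not support them.

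- A reader might infer that a non-significant test would be reported as no excess harm. Nothing in the article says so, and it sets no rule for concluding safety.
- A reader might infer that safety is judged by these tests alone. Arm-level frequencies will be shown, from which a risk difference can be computed, and an independent data safety monitoring board assesses risk and benefit throughout.
- A reader might infer that most relevant harms would be missed. That depends on control rates the article does not give. The Discussion's remark on rarity concerns adverse effects of plasma exchange, not background rates in refractory septic shock.
- A reader might call the lack of a safety margin a defect. Without a safety hypothesis none is needed.
- A reader might want Fisher's exact test instead. Under equal rates of 1% to 20% at 137 per arm, the uncorrected chi-squared test rejects in 2.5% to 5.1% of trials, so it does not inflate error to any relevant degree. Fisher's test would be less sensitive to harm: at 4 against 0 events chi-squared gives p = 0.044 and Fisher p = 0.12.

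**Conclusion.** The point holds as a minor one. Chi-squared tests are the sole named between-arm comparison for all safety endpoints. For endpoints with a control rate of 1% to 5%, they would miss a true doubling in roughly 65% to 92% of trials, and they give no result when there are no events. A p-value alone does not show what excess harm remains compatible with the data. The size rests on assumed control rates, about 137 treated patients per arm, a two-sided 5% level and no continuity correction. The primary conclusion is unaffected.

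**What to change.** Replace the testing clause in Analyses of safety endpoints, or add to the SAP, wording such as: *For each safety endpoint the risk difference (TPE minus SOC) will be reported with a two-sided 95% score (Miettinen-Nurminen) confidence interval. Any p-values are descriptive. A non-significant difference will not be taken as evidence of no harm.*

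No margin and no change to Fisher's test is needed.

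The cost is one or two sentences and a few table columns, with no new data and no extra patients. The downside is that wide intervals will make the safety statement look less reassuring.

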#### Subgroup analyses

Subgroup analyses will be performed for the primary and key secondary endpoints in the relevant subgroups including sex, age (≥ 60/ < 60), pulmonary focus of infection (yes/no), RRT (yes/no), pre-existing congestive heart failure NYHA III/IV (yes/no), pathogen (gram + /gram −), baseline lactate concentration (< 4.5/ ≥ 4.5 mmol/l).

### Oversight and monitoring

#### Responsibilities

This study will be conducted in compliance with the ICH GCP guidelines (as far as possible for this kind of study) and the Declaration of Helsinki. Investigators must have sufficient time to conduct the clinical study in compliance with the study protocol. Furthermore, they have to accurately and completely enter study data in the eCRF. Investigators are responsible for obtaining informed consent of the patients as well as for the preparation and maintenance of adequate case files in order to record observations and other data relevant for this clinical study. Besides, they have to file the study-related records in the ISF and have to maintain its actuality. They will permit study-related monitoring visits. The investigator must provide direct access to the study site’s facilities, to source documents, and to all other study documents.

#### Favorable opinion of independent ethics committee

Study protocol, patient information with consent, and substantial amendments will be assessed by the responsible ethics committees. Favorable opinion of the specific Independent Ethics Committee (IEC) must be available prior to study start at all study sites. The ethical committee of MHH has initially approved the protocol as lead ethical institute in 2015 (No.2786–2015) and has renewed its approval in 2020 (No.8852_MPG_23b_2020) and most recently in 2023 (No. 10607_BO_SK_2022).

#### Monitoring

Monitoring is performed for reasons of quality assurance and to verify that the study is conducted according to the protocol as well as to legal and regulatory requirements applicable for clinical trials. Quality assurance will be based on three components: on-site monitoring, central monitoring, and extensive training. All trial-related processes will follow the SOPs of the Hannover Clinical Trials Center (Zentrum für Klinische Studien (ZKS)). Key documents and processes are subject to internal review, following the SOPs of the ZKS. Central monitoring will include a timely query management process based on consistency and plausibility checks automatically generated from the database, combined with a reminder process for missing documentation. A total of 3 on-site monitoring visits (1 visit/year) will be performed by monitors of the ZKS. Pre-study visits will be performed in each recruiting center via phone by ZKS-independent monitors to instruct the local investigators in how to follow the study protocol and documentation of data. An on-site initiation visit has to be performed, before a site is allowed to start recruitment to ensure adherence with all study procedures by the monitor of ZKS. Periodic monitoring visits and source data verification will be done according to a risk-adapted approach and to assure high data quality and patient safety and to check informed consents. The focus of on-site monitoring will be on the verification of informed consent documents, eligibility criteria, primary endpoint, key secondary endpoints, and safety aspects (100% of the patients included). One hundred percent source data verification will be performed for the first patient of each trial site and for 20% of all further patients, respectively. Close out visits will be done at the end of the trial and in case a site will be closed.

#### Record retention

All relevant study-related documents have to be archived for at least 10 years after completion or premature discontinuation of the clinical study. The investigator agrees to keep the ISF, including the identity of all participating patients, all original signed informed consent forms, detailed records of treatment, all other applicable study-related documents, and source documents. The records should be retained by the investigator for at least 10 years after completion or premature discontinuation of the clinical study. Source data have to be kept according to national regulations.

#### Insurance

The trial will be covered by the trial site`s individual liability insurance (Haftpflichtversicherung). All subjects/legal representatives will be informed about their rights and obligations in regard to insurance policies before participating in the study. A copy of the insurance policies will be handed out to each patient/legal representative.

#### Amendments

Each amendment of essential study documents has to be approved by the study initiators. Favorable opinion of IEC is required for amendments prior to implementation.

#### Dissemination plans

It is anticipated to publish the results of the clinical trial in a scientific medical journal and at national and international meetings. The responsible investigator will designate the first and the last authors of the publication. The order of subsequent authors will be allocated according to the number of patients recruited by each site. The trial was registered at ClinicalTrials.gov (NCT05726825, Registered on 02/14/2023). Data will be available to investigators upon reasonable request.

## Discussion

To the present time, no adequately powered randomized clinical trial has investigated the effect of TPE on survival in septic shock patients. Previous studies investigating TPE in sepsis have either been underpowered or included a heterogenous study population [7, 8]. Therefore, despite promising data demonstrating more rapid hemodynamic stabilization [10, 14], the role of TPE as a potential adjunctive treatment option in septic shock remains unclear. As we have observed the most obvious clinical effects (during the feasibility trial) in sepsis patients that have been treated very early after onset of shock and that demonstrated particularly profound hemodynamic instability, we have designed the inclusion criteria of the here described study accordingly. This effort to homogenize the participants (early and severe septic shock) stands in contrast to previous trials that have investigated a broader range of septic patients.

TPE using human plasma as replacement fluid has potential adverse effects, including infectious and non-infectious (allergic reaction, transfusion associated lung injury (TRALI), citrate toxicity, hypotension) [16] with pruritus and urticaria most commonly observed [17]. However, severe adverse events are extremely rare [18] and incidence of adverse events requiring discontinuation of treatment lies at around 0.2% [17]. Of note, no adverse events were observed in our previous EXCHANGE feasibility pilot study [10] and the randomized EXCHANGE-1 trial, investigating patients with literally the same characteristics [19]. To avoid potential allergic reactions, anti-histamines will be administered before TPE (and in the control group at time of randomization). Importantly, there is no additional invasive exposure of the patient. The central line used for TPE will be inserted for clinical management (e.g., RRT) only and all biosamples will be drawn via catheters (central venous and arterial), which have been placed independent of biosampling for treatment and monitoring indication. Therefore, no additional puncture of the skin needs to be performed for biosampling.

The investigators convinced that a risk–benefit consideration clearly favors performance of the here proposed clinical trial. Importantly, this is an investigator-initiated trial, funded by the DFG without any competing commercial or financial interests involved.

Furthermore, accompanying systematic and longitudinal biosampling together with predefined innovative center-specific research projects will most certainly enable highly stimulating scientific investigations in the field of septic shock research.

